## Abstract

**Background/Objectives**: Most survivors of out-of-hospital cardiac arrest (OHCA) may suffer from cognitive, mental difficulties, and fatigue, which negatively impact their quality of life, despite a good physical recovery. However, no definitive data are available on this topic, so this study aims to assess the feasibility and acceptability of a centralized, sub-regional screening system for OHCA survivors in Italy and the prevalence of these disorders. **Methods**: OHCA survivors discharged with good neurological outcomes (Cerebral Performance Category (CPC) ≤ 2 and modified Ranking Scale (mRS) ≤ 3) from hospitals in the “Lombardia CARe” registry will be evaluated by a clinical psychologist using the Montreal Cognitive Assessment (MoCA), Hospital Anxiety and Depression Scale (HADS), EQ-5D-5L for quality of life, and the Impact of Event Scale-Revised (IES-R) at pre-discharge or within 15 days and then at 1, 3, 6, and 12 months. Patients with clinical issues will be referred for psychological support or to a community rehabilitation program. Feasibility will be defined as a recruitment rate ≥ 80% and acceptability as a retention rate ≥ 50% over 12 months. **Results**: Based on historical data from the Lombardia CARe, an estimated 350 eligible survivors are expected, which will allow estimation of a prevalence ranging between 20% and 30% with 5% precision and 95% confidence. **Conclusions**: This study will be the first in Italy to evaluate the feasibility and acceptability of a centralized, sub-regional system for pre-/post-discharge evaluation of cognitive impairment, mental health, and quality of life in a large cohort of OHCA survivors, documenting the prevalence of these disorders.

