## 1. Introduction

Out-of-hospital cardiac arrest (OHCA) is a leading cause of mortality worldwide, with overall survival rates estimated at 5–10% [1,2]. In Italy, about 60,000 OHCAs occur each year, with an incidence of about 1 case per 1000 inhabitants [3]. Among those who do survive, many achieve a good physical recovery yet may suffer from pronounced emotional or cognitive sequelae (e.g., rates of emotional problems and cognitive impairment at 6 months have been estimated at around 15–30% and 40–50%, respectively), along with fatigue [4,5,6]. These challenges can hinder a return to everyday life for both patients and relatives [7,8,9].

Guidelines from the European Resuscitation Council on the treatment of OHCA emphasize the importance of a systematic follow-up to screen for cognitive and emotional problems—for example, development of anxiety and depression or post-traumatic stress disorder symptoms—and to provide appropriate psychological support for patients and their families [6]. The importance of identifying (and meeting) the care and rehabilitation needs of survivors and their family members has also been recently highlighted by the Resuscitation Council UK [10] and translated for adoption by Fondazione IRC—the Italian non-profit organization dedicated to advancing the science and practice of resuscitation [11]. Some examples of post-discharge follow-up systems have been reported [12,13] alongside a framework for a multidisciplinary, guideline-based approach to improve the cardiac arrest pathway [14]. Guidelines and consensus statements also encourage the creation of multidisciplinary, holistic pathways of assessments and care [15,16,17]. Despite that, few structured programs exist globally, and few are currently in place in Italy. It is currently unclear which framework is best suited to deliver a comprehensive follow-up service that caters to the psychological/cognitive and physical needs of these patients; in addition, each healthcare system has unique implementation challenges. That notwithstanding, resource availability (i.e., personnel able to deliver the service) and access to appropriate training (i.e., how to deliver the service) are likely to be key issues.

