During 2017–2018, the Cardiology Division of the Fondazione IRCCS Policlinico San Matteo, which is the coordinating centre of the Lombardia Cardiac Arrest Registry (LombardiaCARe), in collaboration with a non-profit organization (Pavia nel Cuore ODV) and the Psychiatry Unit of the University of Pavia, promoted a pilot study on the assessment of the psychological and emotional state of out-of-hospital cardiac arrest survivors in the Province of Pavia. This project showed that, in line with international data, more than one-third of patients discharged with a good neurological outcome (mRS ≤ 3) showed symptoms of at least moderate depression [18]. The incidence of depression was also higher in younger patients (<50 years old), in line with other observational studies [19,20,21], with mental health being particularly affected. The health-economic implications of this long-term burden are likely significant.

Building on those pilot data, this study aims to (a) investigate the feasibility and acceptability of a centralized, sub-regional assessment and follow-up system; and (b) to investigate the prevalence of psychological distress, cognitive impairment, and fatigue, as well as the degree of health-related quality of life in a large, multicentre cohort of OHCA survivors.

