### 2.2. Criteria for Feasibility and Acceptability

Feasibility will be defined quantitatively by examining the **recruitment rate** (i.e., the proportion of eligible patients who consent to participate) and the **retention rate** (i.e., the proportion of enrolled patients who complete scheduled follow-up assessments over the 12-month period). In the absence of literature benchmarks and prior pilot data, a pragmatic threshold *of 80% recruitment rate* of eligible patients will be set as a measure of feasibility.

Acceptability will be operationalized as an *overall retention rate of 50% or more of the recruited patients* over 12 months. In addition, this study will look at feasibility and acceptability by follow-up modality, comparing the recruitment and attrition rates between face-to-face assessments at the main hospital and remote assessments at the other hospitals. A significantly lower recruitment rate or higher attrition rate in the remote modality, as compared to the face-to-face approach, will be interpreted as indicative of reduced feasibility and acceptability.

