### 3.2. Identification of Prevalence of Mood Disorders in OHCA Survivors

Based on Lombardia CARe figures, approximately 5200 OHCAs occur yearly in the regional area, and, in about 3500 of them, resuscitation is attempted. Of these, about 600 survive to hospital admission, and about 175 per year are discharged alive with CPC 1–2 or mRS ≤ 3. Therefore, over 24 months, about 350 eligible survivors are expected. Assuming 80% of them consent to be included in this study (about 280), this cohort will be sufficient to identify the presence of symptoms of at least mild anxiety or depression in 25% of cardiac arrest survivors at 6 months from the event, with 5% precision and 95% confidence (Appendix A, Table A2). Although the prevalence of mood disorders after OHCA has been investigated by several studies, REVIVE will be the first one to do so at the sub-regional level in Italy.

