**Intervista clinica semi-strutturata (original italian version)**
**Cognizione e funzioni cognitive:** *“Ha notato cambiamenti nella sua memoria, nella capacità di concentrarsi o nel trovare le parole giuste dopo la dimissione, e in che modo questi cambiamenti influenzano le sue attività quotidiane?”* 2. **Cognizione e funzioni cognitive:** *“Ha notato cambiamenti nella sua memoria, nella capacità di concentrarsi o nel trovare le parole giuste dopo la dimissione, e in che modo questi cambiamenti influenzano le sue attività quotidiane?”* 3. **Benessere emotivo e umore:** *“Nelle ultime settimane, ha provato sentimenti di ansia, umore depresso o ricordi indesiderati legati all’arresto cardiaco? In che modo questi sentimenti hanno influito su di lei o sui suoi familiari?”* 4. **Affaticamento e recupero fisico:** *“Prova stanchezza persistente, difficoltà di mobilità o limitazioni fisiche che rendono le attività di tutti i giorni più impegnative rispetto a prima dell’arresto cardiaco?”* 5. **Vita quotidiana, lavoro e indipendenza:** *“Ha riscontrato difficoltà nel riprendere le attività quotidiane importanti, come guidare, gestire i lavori domestici o tornare al lavoro? Ritiene di avere il supporto necessario per affrontare queste sfide?”* 6. **Informazioni necessarie e reti di supporto:** *“Lei e i suoi familiari sentite di avere le informazioni e il sostegno necessari—ad esempio, comprendete la funzione dei farmaci, sapete cosa aspettavi nei prossimi mesi, e siete in grado di accedere a supporto emotive/di mutuo aiuto—per gestire al meglio questa fase del recupero?”*

**Table A2 jcm-14-03631-t0A2:** Precision of the proportion estimate according to the number of patients enrolled and the proportion found.

Expected Proportion	Absolute Precision with 95% Confidence									
	0.01	0.02	0.03	0.04	0.05	0.06	0.07	0.08	0.09	0.10
**0.01**	381	96	43	24	16	11	8	6	5	4
**0.11**	3761	941	418	236	151	105	77	59	47	38
**0.21**	6373	1594	709	399	255	178	131	100	79	64
**0.31**	8217	2055	913	514	329	229	168	129	102	83
**0.41**	9293	2324	1033	581	372	259	190	146	115	93
**0.51**	9600	2400	1067	600	384	267	196	150	119	96
**0.61**	9139	2285	1016	572	366	254	187	143	113	92
**0.71**	7910	1978	879	495	317	220	162	124	98	80
**0.81**	5913	1479	657	370	237	165	121	93	73	60
**0.91**	3147	787	350	197	126	88	65	50	39	32

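### The 5-point precision for a 6-month prevalence is based on about 280 patients enrolled, with no allowance for loss, and the Abstract attaches a wider claim to 350 eligible patients

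*Protocol article*

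**What the plan says.** Section 3.2 derives the sample from registry figures: about 175 eligible survivors a year, about 350 over 24 months, and 80% consent, giving about 280. It then states that "this cohort will be sufficient to identify the presence of symptoms of at least mild anxiety or depression in 25% of cardiac arrest survivors". The time point is given in the same sentence: "symptoms of at least mild anxiety or depression in 25% of cardiac arrest survivors at 6 months from the event". The precision follows: "with 5% precision and 95% confidence (Appendix A, Table A2").

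Appendix A, Table A2 is headed "Precision of the proportion estimate according to the number of patients enrolled and the proportion found". At a precision of 0.05 it lists 255 patients for a proportion of 0.21 and 329 for 0.31. It has no row for 0.25.

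The Abstract makes a different statement: "an estimated 350 eligible survivors are expected, which will allow estimation of a prevalence ranging between 20% and 30% with 5% precision".

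Three other places bear on how many patients will be seen at 6 months. Section 2.2 sets acceptability at an "overall retention rate of 50% or more of the recruited patients" over 12 months. Section 2.4 plans multiple imputation for missing data but does not impute patients who leave the study altogether; it also prescribes exact 95% confidence intervals for prevalences. The Discussion lists attrition among the limitations and gives no rate.

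**The concern.** A prevalence at 6 months can be estimated directly only from patients assessed at 6 months. Section 3.2 uses the number who consent and deducts nothing for death, withdrawal or a missed visit, although the rest of the article expects some loss.

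The Abstract has a second fault of the same kind. Its base is the number eligible, before the 80% consent assumption that section 3.2 applies, and it claims the precision over a range that reaches 30%, where more patients are needed. Two places in one article therefore support a 5-point claim from two different denominators.

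This is the article's only sample-size justification. Readers will take 5 points as the resolution of the 6-month estimate, and the plan's own numbers do not deliver it once any patient is lost.

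**Working it through.** **Inputs.** From section 3.2: proportion 25%, half-width d = 0.05, 95% confidence, 350 eligible, 80% consent. From the Abstract: 20–30%, d = 0.05, 350 eligible. From section 2.2: 50% retention over 12 months. From section 2.4: exact intervals. No 6-month loss rate is given, so the losses below are assumptions.

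**Step 1: reproduce the plan's figures.** 350 × 0.80 = 280, as stated. Table A2 follows n = 1.96² p(1−p)/d². At d = 0.05, p = 0.21 gives 254.9 (table: 255) and p = 0.31 gives 328.7 (table: 329). The formula matches all 100 cells to within one patient.

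**Step 2: the requirement for the stated claims, d = 0.05.**
- 20%: 3.8416 × 0.16 / 0.0025 = 245.9, so 246
- 25%: 3.8416 × 0.1875 / 0.0025 = 288.1, so 289
- 30%: 3.8416 × 0.21 / 0.0025 = 322.7, so 323

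As shares of the 350 eligible, 289 is 82.6% and 323 is 92.3%. Both exceed the 80% assumed to consent, before any loss to follow-up.

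**Step 3: half-widths on the two bases.** Half-width = 1.96 × √(p(1−p)/n), in percentage points.

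| Prevalence | n = 350 (eligible) | n = 280 (enrolled) |
|---|---|---|
| 20% | 4.19 | 4.69 |
| 25% | 4.54 | 5.07 |
| 30% | 4.80 | 5.37 |

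The Abstract's claim is correct for 350 analysed patients. At 280 it holds at 20% and fails at 30%.

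**Step 4: allow for loss before 6 months.** The exact column is the Clopper-Pearson half-width (half of the interval's length) at an observed 25%.

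| Assessed | Loss from 280 | Normal formula, 25% | Exact, 25% | Normal formula, 30% |
|---|---|---|---|---|
| 280 | none | 5.07 | 5.23 | 5.37 |
| 252 | 10% (assumed) | 5.35 | 5.52 | 5.66 |
| 224 | 20% (assumed) | 5.67 | 5.87 | 6.00 |
| 196 | 30% (assumed) | 6.06 | 6.28 | 6.42 |
| 140 | 50% (12-month acceptability floor) | 7.17 | 7.47 | 7.59 |

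At 70/280 the exact interval is 20.0% to 30.5%; at 35/140 it is 18.1% to 33.0%. The last row is the worst result the plan would still call acceptable at 12 months. It is not a forecast for 6 months.

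**The case against.** Much can be said for the plan.

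- **280 against 289.** A reader might infer an arithmetic error. The documents do not support that. The figures are given as approximate, 5.07 points rounds to 5, and interpolating Table A2 between 0.21 and 0.31 gives 255 + 0.4 × 74 = 284.6. What remains is only that there is no margin to absorb loss.
- **Retention of 50%.** A reader might infer that 140 patients are expected at 6 months. Section 2.2 sets a 12-month threshold for acceptability, and a patient who fails it may still have a 6-month assessment.
- **Imputation.** Multiple imputation may recover some precision for patients who miss a visit but stay in the study. It does not apply to complete withdrawals, so the point is reduced, not removed.
- **Exact intervals.** Sizing with the normal formula and reporting exact intervals is ordinary practice. At 280 the difference is 5.23 − 5.07 = 0.16 points and is no separate error.
- **Planning value.** A reader might infer that 25% is too low, because the pilot found that "more than one-third of patients discharged with a good neurological outcome (mRS ≤ 3) showed symptoms of at least moderate depression". But the Introduction also reports that "rates of emotional problems and cognitive impairment at 6 months have been estimated at around 15–30% and 40–50%, respectively", and 25% lies within the range for emotional problems. The article gives neither the assessment time nor the size of the pilot. Section 3.2 makes no precision claim for cognition.
- **The Abstract.** Its arithmetic is right for 350. The fault is the base.
- **Consequence.** The first aim is feasibility and acceptability, and no test or decision rule rests on 5 points.

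None of this answers two facts: a 6-month estimate is sized on enrolment, and the Abstract counts patients whom the body does not expect to enrol.

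**Conclusion.** The point holds in a limited form. Section 3.2 reaches its stated precision only to rounding, and only if every one of about 280 enrolled patients is assessed at 6 months. The Abstract's claim at the top of its range needs 323 analysed patients, against about 280 expected to consent.

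The shortfall is modest. With exact intervals at 25%, the half-width is about 5.2 points with no loss and 5.5 to 6.3 points for losses of 10% to 30%. Those loss rates are assumptions, and the calculation counts only patients actually assessed, without any gain from imputation.

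The statements should be corrected because they are not delivered by the plan's own numbers. The matter does not threaten the study: exact intervals will be reported whatever number is reached.

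**What to change.** Use the same base in the Abstract and section 3.2. In the Abstract, replace the 350 eligible patients with the number expected to enrol and the number expected to be assessed. In section 3.2, state the retention assumed at 6 months and give the precision for the resulting number.

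Suggested content, using the exact intervals of section 2.4 at 25%: about ± 5.2 points if all 280 are assessed, ± 5.5 at 252, ± 5.9 at 224 and ± 6.3 at 196. If 12-month precision is also quoted, 140 patients give about ± 7.5, labelled as the acceptability floor. Keep to one interval method throughout.

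As optional information, the article could add that outcomes expected at 40–50%, such as cognitive impairment, would have half-widths of about 5.7 to 5.9 points at 280 by the normal formula.

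The cost is wording only. No extra patients and no change of design or analysis are needed; the stated precision becomes slightly less favourable.

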Longitudinal changes in HADS, MoCA, EQ-5D-5L, and IES-R from T0 to T4, as well as differences in the retention rate between patients seen remotely or face-to-face, will be analyzed using mixed-effects models (linear or logistic) incorporating time and potential covariates (e.g., age, sex, comorbidities). Models will initially include random intercepts and slopes at participant and hospital levels. Different residual covariance structures (e.g., first-order autoregressive [AR(1)]) will also be explored. Model selection will be guided by the Akaike Information Criterion (AIC) and Bayesian Information Criterion (BIC); simpler random intercept-only models will be adopted if convergence issues arise. Missing data will be handled using Multiple Imputation by Chained Equations (MICE), assuming a Missing At Random (MAR) mechanism. Twenty imputed datasets will be generated, incorporating all key predictors and outcomes, as well as hospital ID. Participants who completely withdraw from this study will be treated as censored at their last observation without further imputation. Sensitivity analyses comparing complete-case and imputed datasets will be conducted to assess the robustness of the findings. A *p*-value < 0.05 (two-sided) will denote statistical significance.

Qualitative data will be derived from detailed notes taken during semi-structured interviews; the analysis will employ a framework approach, well-suited for applied qualitative research with pre-defined areas of inquiry [29]. The analytic process will involve familiarization with the notes, followed by the development of a thematic framework based on the predetermined domains. Data will then be indexed using both deductive codes—stemming from the interview guide—and emergent codes that may arise from the content of the notes. A matrix will be constructed to chart responses across cases, enabling systematic cross-case comparisons.

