## 4. Discussion

Survivors of OHCA face a broad array of challenges, extending beyond the immediate physical aftermath to include psychological distress, cognitive impairments, and chronic fatigue. Depression is notably associated with higher mortality in this population [31]. Despite increased awareness, however, few structured pathways exist to identify and address these non-physical sequelae. Current pathways involve follow-ups being completed mostly or entirely in person, by the hospital that admitted the patients following their OHCA [12,14]; despite this approach having clear advantages (namely, full access to the clinical history of the patient; patient being already familiar with the hospital/treating team; face-to-face meeting being more accessible to some patients, etc.), it also requires more resources in terms of personnel, training required and clinic space.

The prospective, multicentric REVIVE project aims to investigate the feasibility and acceptability of a centralized, sub-regional system to investigate mood, cognition, fatigue, psychological wellbeing, and overall quality of life at multiple time points up to 12 months post-discharge. It also aims to be the first study to systematically assess psychological distress, cognitive status, and quality of life in a sizable Italian cohort of OHCA survivors.

Study limitations may include attrition (e.g., among patients with cognitive deficits or significant psychological difficulties) and the non-randomized nature of the intervention. Remote/telemedicine follow-up options will aim to reduce dropout; however, they might also constitute a barrier for some patients who feel less comfortable using new technology.

Should the REVIVE study demonstrate the need for a tailored psychological approach and that our approach is feasible and welcomed by the patients, it could serve as a guide to build up similar and permanent programs to help patients thrive and not simply survive after a cardiac arrest.

The results are expected to guide future recommendations on the delivery of follow-up/assessment services and help establish new standards of post-resuscitation care.

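### The ±5-point precision claimed for the 6-month prevalence is computed on patients enrolled, with no allowance for loss before the 6-month visit

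*Protocol article*

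**What the plan says.** Section 3.2 starts from registry volume: "over 24 months, about 350 eligible survivors are expected". It continues: "Assuming 80% of them consent to be included in this study (about 280), this cohort will be sufficient" to find at least mild anxiety or depression "in 25% of cardiac arrest survivors at 6 months from the event, with 5% precision and 95% confidence". For support it points to Appendix A, Table A2, whose title reads "Precision of the proportion estimate according to the number of patients enrolled and the proportion found".

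The Abstract carries a second precision statement. It attaches 5% precision, for prevalences of 20% to 30%, to the 350 eligible survivors, before consent is taken into account.

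Other sections allow for loss after enrolment:

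- Section 2.2 defines acceptability over 12 months as an "overall retention rate of 50% or more of the recruited patients".
- Section 4 concedes that "Study limitations may include attrition", particularly in patients with cognitive or psychological difficulties, and hopes that remote follow-up will reduce dropout.
- Section 2.4 plans multiple imputation by chained equations (20 datasets, missing at random) for missing data, but adds: "Participants who completely withdraw from this study will be treated as censored at their last observation without further imputation".

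**The concern.** The quantity being sized is a prevalence at a follow-up visit, so its precision depends on how many patients provide data at that visit. Section 3.2 takes the number who consent and uses it as the number analysed. No step between enrolment and 6 months reduces it, although three other sections treat loss as something to be measured, tolerated or handled.

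Estimating prevalence is one of the two stated aims, and this calculation is the article's quantitative support for the cohort size under that aim. A reader who relies on it will expect a narrower 6-month interval than the study will give once any patient is lost.

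**Working it through.** **Inputs.** Eligible: 350 (section 3.2, 175 per year for 2 years). Consent: 80%, so 350 × 0.80 = 280. Prevalence p = 0.25, half-width d = 0.05, 95% confidence (section 3.2). Interval method for the analysis: exact (section 2.4). The completion rate at 6 months is not given; the rates below are assumptions.

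**Reproducing the plan's method.** The Wald formula n = z²p(1−p)/d² with z = 1.96, rounded up, reproduces Table A2. In the 0.05 column, for example, p = 0.21 gives 254.9 (table: 255) and p = 0.31 gives 328.7 (table: 329). The table has no row for 0.25.

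**The plan's own claim.** At p = 0.25 and d = 0.05, n = 1.96² × 0.1875 / 0.0025 = 288.1, so 289 assessed. In the other direction, 280 assessed gives 1.96 × √(0.1875/280) = 5.07 points. The stated 5% therefore reproduces to rounding, provided that all 280 are assessed.

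**Allowing for loss.** Half-width = 1.96 × √(0.1875/n), next to the exact 95% interval when 25% of those assessed are positive:

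| Assumed share assessed | n | Wald half-width (points) | Exact 95% interval |
|---|---|---|---|
| 100% | 280 | 5.07 | 20.0% to 30.5% |
| 90% | 252 | 5.35 | 19.8% to 30.8% |
| 80% | 224 | 5.67 | 19.5% to 31.2% |
| 70% | 196 | 6.06 | 19.1% to 31.7% |
| 50% (lower bound) | 140 | 7.17 | 18.1% to 33.0% |

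The last row is 7.17/5.07 = 1.41 times the width with no loss.

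**Enrolment that would keep 289 assessed.** 289/0.9 gives 322, 289/0.8 gives 362 and 289/0.7 gives 413. The last two exceed the 350 eligible, and all three exceed 280. This shows that there is no reserve; it is not a proposal to enrol more.

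**The Abstract.** With n = 350 the half-widths at p = 0.20, 0.25 and 0.30 are 4.19, 4.54 and 4.80, so the Abstract's claim holds if every eligible patient is both enrolled and assessed. With n = 280 they are 4.69, 5.07 and 5.37. The upper end of the stated prevalence range is already beyond 5 points before attrition.

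**The case against.** Several points on the other side carry weight.

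- **The 50% mark is not a forecast.** A reader might infer that the plan itself expects 140 patients at 6 months. It does not: 50% is a pass mark for acceptability over 12 months. Nor does 140 at 12 months follow from it. Section 2.2 measures retention by completion of the scheduled assessments, so if that means the whole schedule, a patient who misses one visit is not retained but may still be assessed at 6 or 12 months. The 140 row is a lower-bound case under one reading.
- **Imputation.** Patients who miss the 6-month visit without withdrawing would be imputed, so the number analysed is not simply the number assessed. That stands, but imputation from other visits recovers only part of the lost information, and complete withdrawals are not imputed.
- **Rounding and the choice of 25%.** A reader might infer that ±5 is out of reach even with no loss, because 289 exceeds 280. That is too strong: 5.07 rounds to 5, and the text says about 280. To the nearest whole point even 5.35 rounds to 5, whereas 5.67 does not. At a prevalence of 20%, 246 assessed (88% of 280) would be enough; at 30%, 323 would be needed.
- **Strength of the attrition statement.** Section 4 says that limitations may include attrition. It does not predict a rate.
- **Consequences.** This is an observational cohort of consecutive survivors, so registry volume sets the number enrolled. No test or feasibility criterion depends on ±5 points, and exact intervals will be reported at every visit, so the precision achieved will be visible.

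These points limit the size and seriousness of the finding. None of them supplies the missing attrition step.

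**Conclusion.** The claim in section 3.2 holds, nominally, only if every enrolled patient is assessed at 6 months, and the rest of the article does not assume that. At the stated 25%, assumed completion of 90% to 70% gives half-widths of 5.35 to 6.06 points. The lower-bound case of 140 assessed gives 7.17, with an exact interval of 18.1% to 33.0% for 35/140. These figures rest on the plan's own Wald formula, on assumed completion rates, and on no credit for imputation, which would narrow the gap in part. The Abstract has the same weakness one step earlier, because it uses eligible patients as the base.

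The documents do not support the conclusion that the study is too small or cannot report a useful prevalence. The stated precision is too favourable for the visit it names. This should be fixed, as a correction to the wording.

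**What to change.** In section 3.2, replace the sufficiency statement with precision by number assessed. For example: with about 280 enrolled and an assumed 70% to 90% assessed at 6 months (196 to 252 patients), a prevalence of 25% would be estimated with a 95% half-width of about 6.1 to 5.3 points; if only 140 were assessed, a lower bound, about 7.2 points. State that the completion rates are assumptions.

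Put the Abstract on the same basis instead of on 350 eligible survivors. Retitle Table A2 so that its entries are patients assessed at the visit, and add a row for 0.25, the prevalence the text uses.

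The cost is wording in three places and a less favourable stated precision. Recruitment, visits and analyses do not change.
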